## Abstract

**Aims:**

To compare ischaemia-driven complete coronary revascularisation by percutaneous coronary intervention (PCI) with usual care in patients with non-ST-elevation myocardial infarction (non-STEMI) and multivessel disease (MVD).

**Methods:**

The South Limburg Myocardial Infarction (SLIM) trial (NCT03562572) is an investigator-initiated, prospective, multicentre, randomised controlled trial that compares fractional flow reserve (FFR)-guided complete revascularisation during the index procedure with usual care in non-STEMI patients with MVD. A total of 414 patients will be randomised in a 1:1 fashion. The primary endpoint is the composite of all-cause mortality, non-fatal myocardial infarction, and any revascularisation and stroke (MACCE) at 12 months. The secondary endpoints are: MACCE at 24 and 36 months, and the composite of cardiac death, myocardial infarction, any revascularisation, stroke, major bleeding and left ventricular ejection fraction below 45% at 12, 24 and 36 months. Furthermore, quality of life will be assessed by the Patient Health Questionnaire (PHQ-9) and the Short Form (36) Health Survey (SF-36) at 1 and 12 months of follow-up.

**Conclusion:**

The SLIM trial aims to provide evidence whether FFR-guided complete revascularisation by PCI is superior to usual care with respect to clinical outcomes (major adverse cardiovascular events) in non-STEMI patients with MVD.

## Introduction

Patients with ST-elevation myocardial infarction (STEMI) and multivessel disease (MVD) have a worse prognosis than STEMI patients with single-vessel disease [1]. Several randomised clinical trials and meta-analyses have shown that, compared with infarct-related artery only PCI (IRA-PCI), multivessel percutaneous coronary intervention (MV-PCI) resulted in fewer major adverse cardiovascular events (MACE), mainly driven by a reduction in repeat revascularisation [2–5].

Compared with STEMI patients, patients with non-ST-elevation myocardial infarction (non-STEMI) have a higher risk profile, a higher incidence of MVD and less favourable outcome [6, 7]. However, there is no clear evidence regarding the role of ischaemia-driven complete coronary revascularisation by PCI in patients with non-STEMI during the index procedure. Furthermore, both the American and the European guidelines are unclear as to which coronary revascularisation strategy is preferred in non-STEMI patients with MVD [8, 9].

Previous studies showed that MV-PCI in non-STEMI patients reduces follow-up revascularisation rates without affecting MACE [10–12]. However, others also found MACE reduction after MV-PCI [13, 14]. In the SMILE (Survival of Myocardial Infarction Long-term Evaluation) trial, MV-PCI during the index procedure in non-STEMI patients with MVD was superior to multistage PCI during the index hospitalisation in terms of major adverse cardiovascular and cerebrovascular events (MACCE). This was mainly due to repeat coronary revascularisation, without a significant effect on cardiac death and reinfarction [14]. In the above-mentioned trials, assessment of lesion severity was mostly performed visually and fractional flow reserve (FFR) measurements were only performed in approximately 25% of the patients.

Currently, FFR-guided revascularisation has become the standard for in-catheterisation laboratory assessment of flow-limiting lesions in patients with stable angina, but has also been shown to be reliable in patients with unstable angina and non-STEMI [15–17]. The beneficial effect of FFR-guided MV-PCI compared with standard angiography was proven in the large randomised, multicentre FAME (Fractional Flow Reserve Versus Angiography for Multivessel Evaluation) study [18, 19]. In that study, it was demonstrated that all types of adverse events were decreased by 30% in the 1st year after PCI when guided by FFR. The information provided by FFR is similar to that obtained with myocardial perfusion studies. However, it is more specific and masking of one ischaemic area by another, more severely ischaemic, zone is avoided since every artery or segment is analysed separately [20, 21]. In addition, FFR-guided revascularisation has been shown to be cost-effective [22]. A recent study has shown that FFR can reliably assess the haemodynamic severity of non-culprit coronary artery stenosis during the acute phase of STEMI [23]. Therefore, FFR may offer the same advantages in the decision-making process on revascularisation of the non-culprit artery in patients presenting with non-STEMI, similarly as in stable coronary syndromes.

Taking the above into consideration, we expect that ischaemia-driven (FFR) complete percutaneous revascularisation of all significant stenoses in lesions of non-culprit arteries performed within the index PCI procedure will improve clinical outcomes compared to the usual care, guided by the discretion of the physician.

## Methods

### Study design

The South Limburg Myocardial Infarction (SLIM) trial is an investigator-initiated, multicentre, prospective, randomised clinical trial in non-STEMI patients with multivessel coronary artery disease amenable to treatment with PCI, in which 414 consecutive patients will be randomised in a 1:1 fashion, after completion of a successful culprit lesion PCI. In the IRA-PCI the identification of the culprit vessel will be performed according to electrocardiographic, echocardiographic and angiographic parameters as stated in the ESC guidelines [24]. The use of anatomic (intravascular ultrasound or optical coherence tomography) or functional (FFR) imaging modalities to assess the culprit lesion, or to rule out other mechanisms such as dissection or haematomas, will be left to the operator’s discretion. A patient will be excluded if the culprit artery is uncertain. Radial access will be strongly recommended for performance of coronary angiography and PCI.

All patients from June 2018 who present with at least one lesion with a stenosis of approximately 50% or more in a non-IRA with a diameter of ≥2.0 mm and fulfil the inclusion and exclusion criteria will be enrolled. Inclusion and exclusion criteria are listed in Tab. 1. The estimated duration of enrolment is 3 years. An overview of the trial is presented in Fig. 1.

**Table 1 Tab1:** Inclusion and exclusion criteria

Inclusion criteria	Exclusion criteria
Age between 18 and 85 years	Left main coronary artery disease (stenosis >50%)
Presenting with non-STEMI, to be treated with PCI of culprit lesion	Chronic total occlusion of a non-IRA
Presence of at least one stenosis of >50% in a non-IRA on QCA or visual estimation of baseline angiography	Complicated IRA treatment, e.g. extravasation, permanent no reflow after IRA treatment (TIMI flow 0–1) and inability to implant a stent
Non-IRA stenosis amenable for PCI treatment (operator’s decision)	Indication for or previous coronary artery bypass grafting
Able and willing to give signed informed consent	Known severe cardiac valve dysfunction requiring surgery or TAVI in follow-up period
	Killip class III or IV during completion of culprit lesion treatment
	Uncertain culprit lesion
	Life expectancy of <1 year
	Intolerance to aspirin, clopidogrel, prasugrel, ticagrelor or heparin
	Gastrointestinal or genitourinary bleeding in previous 3 months
	Planned elective surgical procedure necessitating interruption of P2Y12 inhibitors during first 6 months post-enrolment
	Currently enrolled in another clinical trial
	Pregnancy
	Expected loss to follow-up

*IRA* infarct-related artery, *PCI* percutaneous coronary intervention, *STEMI* ST-elevation myocardial infarction, *TAVI* transcatheter aortic valve implantation, *TIMI* thrombolysis in myocardial infarction, *QCA* quantitative coronary angiography

**Fig. 1 Fig1:**
[figure not shown]
Randomisation procedure. *FFR* fractional flow reserve, *Non-IRA* non-infarct-related artery, *Non-STEMI* non-ST-elevation myocardial infarction, *PCI* percutaneous coronary intervention

The study has been approved by the Medical Ethical Committee of Zuyderland Medical Centre, The Netherlands. The SLIM trial is registered at ClinicalTrials.gov (NCT03562572) and the Netherlands Trial Register (NTR7158).

### Informed consent and randomisation

Informed consent will be obtained according to the Good Clinical Practice guidelines. To participate in the trial, the participant must give oral approval before randomisation in the presence of a third independent (not involved in the study) person (catheterisation laboratory personnel or a nurse) after successful PCI of the culprit. To avoid a further delay in treatment, a signature will be obtained after full completion of the procedure irrespective of the treatment allocation, but must be obtained before the patient leaves the catheterisation laboratory. If angiographic inclusion criteria are met (presence of at least one stenosis of >50% in a non-IRA with a diameter of ≥2.0 mm) and PCI of the IRA is successful, the patient will be randomised via an online randomisation tool. If the patient is randomised to the usual care group, he or she will be informed that all intermediate lesions will be discussed in the heart team as to whether or not additional revascularisation of the non-IRA arteries will be performed. All patients will receive medical treatment based on current guidelines.

### Ischaemia-driven complete revascularisation group

In the ischaemia-driven complete revascularisation strategy group all flow-limiting (FFR ≤0.80) lesions will receive treatment by PCI and stenting. The non-IRA PCI should be performed during the same intervention. Exceptions can be made for complex lesions where the operator estimates that the revascularisation procedure will require significant contrast overload, which may lead to deterioration of cardiac and renal function of the patient. In such cases, a second procedure should be performed, which should take place within the same hospitalisation, preferably within 72 h.

### Usual care group

In the randomised to usual care group the procedure will stop after the PCI of the culprit artery and the patient will be referred to his/her treating cardiologist and/or heart team. They will decide whether or not (ischaemia-driven) staged PCI of the non-IRA arteries should take place. The following treatment options are possible: (1) FFR- or iFR- (instantaneous wave-free ratio) guided PCI of the non-IRA arteries, (2) additional non-invasive tests, (3) symptom-driven PCI of the non-IRA arteries, or (4) optimal medical therapy. If the treating cardiologist (after consulting the heart team) decides to perform the non-IRA PCI revascularisation, then such treatment should take place within 6 weeks of the primary PCI in order to count as a scheduled staged PCI procedure. Any other revascularisations of any lesions after these 6 weeks are identified as unscheduled and therefore counted as an event.

All revascularisation procedures will be defined as clinically indicated or not clinically indicated by the independent clinical events committee.

## Study endpoints

### Primary endpoint

Primary study endpoints are defined as the incidence of MACE (composite endpoint of all cause death, non-fatal myocardial infarction, any revascularisation and stroke) at 12 months.

### Secondary endpoints

Primary endpoint in subgroups at 12 and 24 months.Composite endpoint of net adverse clinical events defined as composite endpoint of cardiac death, myocardial infarction, any revascularisation, stroke and major bleeding at 12, 24 and 36 months.Composite endpoint hospitalisation for heart failure and unstable angina pectoris at 12, 24 and 36 months.All-cause mortality or myocardial infarction at 12, 24 and 36 months.Any revascularisation at 12, 24 and 36 months.Stent thrombosis at 12, 24 and 36 months.Bleeding (major and minor) at 48 h and 12 months.Primary endpoint at 36 months as well as outcomes of each component of the primary endpoint at 12 and 24 and 36 months.Left ventricular ejection fraction below 45% at 12, 24 and 36 months (myocardial perfusion scintigraphy, magnetic resonance imaging or echocardiography).Quality of life at 1 and 12 months measured by the Patient Health Questionnaire (PHQ-9) and the Short Form (36) Health Survey (SF-36)

## Follow-up

For endpoint adjudication office-based direct visits will be performed at 1 and 12 months, and telephone-based interviews will be performed at 24 and 36 months. At 1 and 12 months of follow-up, quality of life will be evaluated by the PHQ‑9 and the SF-36.

## Statistical analysis

### Sample size calculation and statistical power analysis

The event rates for both groups were defined as follows:

In the usual care group, the event rates are estimated based on data from our previous all-comers registry [7] and the SMILE trial [13]. Rates of MACE in the ischaemia driven group are estimated based on the results of the SMILE trial [13].

In order to assess the superiority of MV-PCI over IRA-PCI, we assume the incidence of MACE to be 20% in the IRA-PCI group and 10% in the ischaemia-driven MV-PCI group. On the basis of a two-sided test size of 5% and a power of 80%, it is calculated that a minimum of 197 patients is needed to be recruited in each group to detect a 10% difference in the incidence of MACE at 1 year. To account for 5% loss to follow-up, a total of 414 (394/0.95) patients will be recruited.

The primary analysis is an intention-to-treat analysis of all randomised patients. A per-protocol analysis will also be performed. All continuous variables will be expressed as mean ± SD and analysed by the Student’s *t*-test. Categorical variables will be analysed by the chi-square or Fisher exact test, as appropriate. Baseline variables with non-Gaussian distributions will be compared using the Mann-Whitney U test and summarised with medians and interquartile range. For the primary endpoint and its components, 95% confidence intervals will be reported. The event-free survival curve for MACE will be constructed using the Kaplan-Meier method, and statistical differences between curves will be assessed by the log-rank test. The hazard ratio for treatment comparisons will be estimated using Cox proportional hazard models. Mean scores of the health-related quality of life will be compared between groups using the independent *t*-test. Statistical analysis will be performed with SPSS (version 15.0, SPSS, Chicago, IL, USA). An independent endpoints committee blinded to the randomisation group will adjudicate clinical study endpoints.

Descriptive analyses of primary outcomes will be performed for the following pre-specified subgroups:Diabetic patients versus non-diabetic patientsElderly (≥75 years) versus young patients (<75 years)Male versus female genderHigh- (GRACE >140) versus low-risk (GRACE ≤140) patients according to Global Registry of Acute Coronary Events (GRACE) risk scorePatients with previous myocardial infarction versus patients with no previous myocardial infarction

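### The analyses named for 12-month MACE make no use of baseline risk factors the trial must collect anyway; pre-specified adjustment would be a small, cheap gain in efficiency

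*Protocol article*

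**What the plan says.** All of this is in the protocol article, Statistical analysis, under the sample size heading.

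- Binary outcomes: "Categorical variables will be analysed by the chi-square or Fisher exact test, as appropriate".
- Time to MACE: Kaplan-Meier curves compared by the log-rank test, with no strata named.
- Effect estimate: "The hazard ratio for treatment comparisons will be estimated using Cox proportional hazard models". No covariates are named, and the model is not described as unadjusted.
- Subgroups: diabetes, age (cut at 75 years), sex, GRACE score (cut at 140) and previous infarction are pre-specified. The only use stated for them is descriptive.
- Sample size: "we assume the incidence of MACE to be 20% in the IRA-PCI group and 10% in the ischaemia-driven MV-PCI group", from which "a minimum of 197 patients is needed to be recruited in each group to detect a 10% difference". Then: "To account for 5% loss to follow-up, a total of 414 (394/0.95) patients will be recruited". This is a plain two-proportion calculation that assumes no gain from baseline information.

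**The concern.** Chi-square, Fisher and an unstratified log-rank test are unadjusted by construction, and the Cox sentence lists nothing beyond treatment. Meanwhile the subgroup list commits the trial to collecting several candidate prognostic factors, one of which is a risk score. Using a few of them in the estimate of the treatment effect would usually give a somewhat more powerful test. It would also protect the result against chance differences in baseline risk between two arms of about 200.

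This has some weight here because the design has little reserve. After the planned 5% loss, 414 × 0.95 = 393.3 patients remain against 394 required. About 59 events are expected, so power falls below 80% if the true difference is smaller than 10 points.

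**Working it through.** **1. The plan's own figure.** Inputs from the article: 20% versus 10%, two-sided 5%, 80% power, 1:1 allocation.

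- Unpooled formula: n = (1.960 + 0.842)² × (0.20×0.80 + 0.10×0.90) / 0.10² = 196.2, so 197 per group. This matches.
- The pooled-variance formula gives 199, within 3%.
- Loss to follow-up: 394 / 0.95 = 414.7, against 414 stated. The difference is immaterial.
- Power at 197 per group is 80.2% (unpooled), 79.6% (pooled) or 80.4% (exact power of the chi-square test). The unadjusted comparison delivers what the article claims.
- Expected events: 197×0.20 + 197×0.10 = 39.4 + 19.7 ≈ 59.

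**2. Adjustment on the risk-difference scale.** Let R² be the assumed share of outcome variance explained by the baseline factors. The variance is then multiplied by (1 − R²):

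power = Φ(0.10 / √[0.25 × (1 − R²) / 197] − 1.960)

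| Assumed R² | Power at 197 per group | n per group for 80% |
|---|---|---|
| 0 | 80.2% | 197 |
| 0.01 | 80.6% | 195 |
| 0.02 | 80.9% | 193 |
| 0.05 | 82.1% | 187 |
| 0.10 | 84.1% | 177 |

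**3. Adjustment in a Cox model.** Two separate simulations (A and B) used 197 patients per arm, exponential event times, censoring at 12 months, marginal 12-month risks held at 20% and 10%, and Wald tests, with 3,000 to 4,000 trials per setting. The c-statistic is an assumption throughout. The Monte Carlo standard error of each power is about 0.6 points at 4,000 trials.

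| Assumed c-statistic | Unadjusted | Adjusted | Gain (points) |
|---|---|---|---|
| Not prognostic (B) | 78.9% | 78.9% | 0 |
| 0.59, one score (B) | 79.6% | 80.1% | 0.5 |
| 0.62, one score (A) | 80.1% | 80.8% | 0.7 |
| 0.64, three factors (A) | 78.4% | 79.6% | 1.2 |
| 0.66, one score (A) | 79.4% | 81.7% | 2.3 |
| 0.67, one score (B) | 80.3% | 81.4% | 1.1 |
| 0.71, one score (A) | 78.8% | 82.8% | 4.0 |
| 0.72, one score (B) | 79.4% | 82.9% | 3.5 |
| 0.77, one score (A) | 80.0% | 86.8% | 6.8 |
| 0.77, one score (B) | 80.5% | 87.2% | 6.7 |

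The three-factor row assumes hazard ratios of 1.5 per SD of GRACE, 1.5 for diabetes and 1.4 for previous infarction. Its gain is worth about 3% more patients; the gain at 0.71 is worth about 11%. With equal 15% risks in both arms, type I error in the three-factor setting was 5.0% unadjusted and 4.5% adjusted.

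**4. Chance imbalance.** With 207 per arm and an assumed 25% prevalence of a binary risk factor, the 95% range of the between-arm difference is ±1.96 × √(2 × 0.25 × 0.75 / 207) = ±8.3 percentage points.

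**5. Room for covariates.** Treatment plus three covariates is four parameters: 59 / 4 ≈ 15 events each.

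**The case against.** The strongest objection is that nothing here is wrong. An unadjusted comparison of randomised arms is valid, held its type I error in simulation and is the analysis the sample size was built for. That stands, and it rules out calling this an error.

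A reader might go further than the documents allow in four ways.

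- *That the plan fixes an unadjusted Cox model.* The sentence does not say so. A journal article commonly leaves the covariate list to an analysis plan, and that plan is not shown. Only the chi-square, Fisher and log-rank tests are unadjusted as named.
- *That the factors are recorded for every patient.* The subgroups imply that they will be collected. Completeness is not stated.
- *That adjustment costs nothing.* It changes the meaning of the hazard ratio, needs a rule for missing values and is limited by the number of events.
- *That the unadjusted hazard ratio is biased towards 1.* The marginal and conditional hazard ratios are different quantities. Most of the gap between them reflects non-collapsibility.

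The gain may also sit at the low end. The Introduction reports that the advantage in the cited SMILE trial came chiefly from repeat revascularisation, and the sample size takes its rates partly from that trial. In the usual care group, non-culprit revascularisation is decided by the cardiologist or heart team and counts as an event after 6 weeks. Nothing in the article shows that GRACE, diabetes or previous infarction predicts that decision.

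What survives is narrower: pre-specified adjustment lost no power in these runs even with a non-prognostic covariate, and it uses data the trial plans to hold.

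**Conclusion.** This is an optional efficiency improvement. The stated design is valid and has its 80% power without adjustment. Adjusting for a few pre-specified baseline factors would add roughly 0.5 to 4 points of power if their c-statistic for MACE is about 0.59 to 0.72. For GRACE, diabetes and previous infarction together, at 0.64, it would add about 1 point. Gains near 7 points need a c-statistic of about 0.77, which nothing in the documents supports. If the factors do not predict MACE the gain is nil, and it shrinks if revascularisation dominates the composite. All of these sizes rest on assumed prognostic strength.

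Adjustment would not rescue the trial if the 10-point difference is optimistic. Its second benefit, protection against chance imbalance, depends on choosing the factors in advance.

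**What to change.** Before unblinding, state in one sentence that the treatment effect on 12-month MACE is estimated with adjustment for continuous GRACE score, diabetes and previous infarction. Choose one of two routes:

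- a Cox model of time to first MACE, censored at 12 months; or
- a logistic model followed by standardisation, which keeps the 12-month risk difference on which the sample size rests.

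Report the unadjusted result and the Kaplan-Meier curves alongside. If the analysis plan already says this, no change is needed.

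The cost is that sentence, and no new data beyond what the subgroups require. The downsides should be accepted openly. An adjusted Cox hazard ratio is conditional on the covariates and differs from the marginal one. Missing baseline values need a simple rule fixed in advance, such as single imputation. About 59 expected events allow only a few covariates, so the list should stay short.

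### The independent t-test fixed for PHQ-9 and SF-36 cannot use 1-month scores when 12-month scores are missing: a small cost at the planned 5% loss, larger if missingness differs by arm

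*Protocol article*

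**What the plan says.** Quality of life is a secondary endpoint. The Secondary endpoints section lists "Quality of life at 1 and 12 months measured by the Patient Health Questionnaire (PHQ-9") and the SF-36. The Follow-up section ties collection to the clinic schedule: "office-based direct visits will be performed at 1 and 12 months", and "At 1 and 12 months of follow-up, quality of life will be evaluated by the" two questionnaires. No baseline score is listed.

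The analysis is stated under Sample size calculation and statistical power analysis: "Mean scores of the health-related quality of life will be compared between groups using the independent" t-test. The general rule in the same paragraph agrees: "All continuous variables will be expressed as mean ± SD and analysed by the" Student's t-test. No repeated-measures term or covariate is named for these scores.

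The only loss figure is in the sample size: "To account for 5% loss to follow-up, a total of 414 (394/0.95) patients will be recruited". It is not split by arm, and no separate rate is given for missing questionnaires.

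**The concern.** An independent t-test takes one value per patient. Applied at 12 months, it drops anyone without a 12-month score, including patients whose 1-month score is on file. That earlier score is likely to predict both the 12-month value and whether the patient attends at 12 months, so discarding it loses information.

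Missingness that differs by arm is plausible here. Treatment is not masked: patients allocated to usual care are told that their remaining lesions go to the heart team. The questionnaires are tied to office visits, which sicker patients may miss. The trial also assumes different 12-month event rates, 20% v 10%. At stake are the accuracy and precision of the 12-month quality-of-life comparison. The primary endpoint is untouched.

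**Working it through.** **The plan's own figure.** The article gives no SD, effect or power for quality of life. Its sample size is for the primary endpoint ("On the basis of a two-sided test size of 5% and a power of 80"%). It reproduces with the unpooled normal formula: (1.960 + 0.842)² × (0.20×0.80 + 0.10×0.90) / 0.10² = 7.85 × 25 = 196.2, so 197 per arm; 394/0.95 = 414.7, stated as 414. That gives 207 randomised per arm, which is used below.

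**Assumptions (none is in the article).** Scores are in SD units with higher meaning better. The correlation between visits is 0.6. Every patient has a 1-month score. The log-odds of a missing 12-month score fall by 1 per SD of the 1-month score.

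**Step 1: shift in one arm's observed mean.** Let p be a patient's probability of being missing and m its average. With a normal 1-month score, the observed 12-month mean is too favourable by 0.6 × E[p(1−p)]/(1−m). This cannot exceed 0.6 × m.

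| Missing | Ceiling 0.6m | Shift |
|---|---|---|
| 5% | 0.030 | 0.028 |
| 10% | 0.060 | 0.055 |
| 15% | 0.090 | 0.080 |
| 20% | 0.120 | 0.104 |

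**Step 2: bias in the between-arm difference, no treatment effect.**
- 5% v 5%, or 15% v 15%: the shifts cancel, bias 0.00.
- 10% v 5%: 0.055 − 0.028, about 0.03 SD.
- 20% v 10%: 0.104 − 0.055, about 0.05 SD.

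For scale, the standard error with 197 per arm is √(2/197) = 0.10 SD.

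**Step 3: false positives at 20% v 10%.** Observed numbers are 207×0.80 = 165.6 and 207×0.90 = 186.3. SE = √(1/165.6 + 1/186.3) = 0.107, and 0.049/0.107 = 0.46. The rejection rate is Φ(−1.96+0.46) + Φ(−1.96−0.46) = 0.067 + 0.008, about 7.5%. Simulations with 200 or 207 per arm gave 6.9% to 7.9%. A likelihood analysis of both visits stayed at about 5%.

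**Step 4: true effect of 0.3 SD, same process in both arms.** The better-off arm then loses fewer patients, so its mean is flattered less and the difference shrinks.
- 5% missing: the t-test estimates about 0.293 SD. SE = √(2/(207×0.95)) = 0.101; power = Φ(0.293/0.101 − 1.96), about 83%. The two-visit analysis estimates about 0.300 SD. Its SE is approximately √[(2/207)(1 + (0.05/0.95)(1 − 0.6²))] = 0.100, and power is about 85%.
- 15% missing: simulation gives 0.286 SD and 78% power for the t-test, against 0.301 SD and 82%.

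If instead the two arms are forced to have exactly the same missing rate despite the effect, the attenuation disappears. It comes from the same dropout rule acting on different scores.

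**Step 5: limit of the remedy.** If dropout follows the unseen 12-month score, the two-visit analysis removes only part of the bias: 0.08 falls to 0.06 SD at 20% v 10%, and 0.04 to 0.03 SD at 10% v 5%.

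**The case against.** An unadjusted t-test between randomised arms is an ordinary and valid default. The only loss rate in the article is 5%, the questionnaires are collected at scheduled visits, and at that rate the choice of method barely matters. All of this stands, and it holds the point to minor. The 5% is planned loss to follow-up, however, and missing questionnaires can exceed it, though the article does not say that they will.

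It can also be objected that handling of missing scores and deaths belongs in the full protocol or analysis plan. That is right, and its absence here is no finding. The point rests only on the test that the article names.

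Two stronger readings are tempting:
- A reader might infer that the comparison is biased whenever worse-off patients are the ones missing. Step 2 shows otherwise: with no treatment effect and the same process in both arms, only the arm means shift.
- A reader might infer a serious excess of false positives. A rate of about 12% does arise if 15% are missing and dropout follows the 1-month score in one arm only. Nothing in the article suggests that pattern or that rate.

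Nor does the article say that only returned questionnaires are analysed. That is how a t-test behaves by default, not a stated rule: "The primary analysis is an intention-to-treat analysis of all randomised patients" is written for the primary analysis.

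**Conclusion.** The concern holds in a limited form. The named t-test discards 1-month scores that are already collected. The 12-month comparison can be biased if missingness differs by arm, which is plausible in an unmasked trial but not quantified in the article. A true effect is slightly attenuated, with some loss of power, even under a common dropout process.

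At the planned 5% loss the cost is about 0.007 SD and 2 percentage points of power, with no bias under the null when the process is common. It reaches about 0.05 SD and 7 to 8% false positives only at 20% v 10% missing. These sizes depend on the assumed correlation and dropout slope. The endpoint is secondary, so the severity is minor.

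**What to change.** For each quality-of-life score, replace the independent t-tests with one mixed model for repeated measures on the 1- and 12-month values. Include arm, visit and arm-by-visit, with an unstructured within-patient covariance. Report the 12-month arm difference with its 95% confidence interval as the quality-of-life result.

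The cost is a sentence of analysis wording and slightly more analysis work; no new data are needed. The model assumes that scores are missing at random given the 1-month score. It recovers nothing for patients missing both visits, and it does not resolve deaths before 12 months. A sensitivity analysis giving patients who died the worst score is optional; it answers a different question and should be labelled as such.
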